# Study Design

## Trial participants

Our trial population will consist of patients with alcohol-related liver cirrhosis Child-Pugh score B or C and ascites, who in one of the involved departments are planned to be offered a liver vein catheterisation for assessment of hepatic venous pressure gradient (HVPG), according to local guidelines.

The sub investigator at the referring centre is a trained physician that handles the patient’s daily treatment. The sub investigator will identify patients in need of liver vein catheterisation and for whom it could be relevant to participate in the trial and who meet inclusion criteria.

Both newly referred patients and patients with a history of cirrhosis will be offered inclusion in the study.

## Inclusion criteria

- Patients with decompensated liver cirrhosis and ascites, verified by ultrasound or CT scan within the last 3 months
- Age between 18 and 80 years.
- Portal hypertension and a hepatic venous pressure gradient (HVPG) of 10 mmHg or more.
- Women of child-bearing age should use safe anti conception, defined as either hormonal anti conception or intrauterine device.

## Exclusion criteria

- Child-Pugh Score above 13
- Clinical signs of infection evaluated by blood biochemistry, urine culture and if applicable ascites puncture, and through clinical assessment by the investigator.
- Received antibiotic treatment within 14 days prior to inclusion
- Presence of hepatocellular carcinoma
- Ongoing invasive cancer or invasive cancer within the last five years,
- Overt hepatic encephalopathy (HE above grade 1),
- Serum creatinine > 200 mol/l,
- Transfusion requiring bleeding within one week prior to inclusion,
- Severe cardiac, pulmonary or kidney diseases or Type 1 diabetes mellitus,
- Continuous alcohol abuse with symptoms of abstinences
- Expected survival less than 3 months,
- Denied consent
- Plasma haemoglobin of less than 5,5 mmol/L

## Withdrawal of trial participants

Trial participants are withdrawn from the study if they:

- Are in need of other antibiotics during study period,
- Are admitted to hospital for other morbidity and require treatment that is incompatible with continuous rifaximin treatment.
- If blinding is repealed.
- Experience deterioration in hepatic encephalopathy above grade 1 or develops hepatic encephalopathy, which will prevent further participation in the trial.

## Dropout

A trial participant will be classified as dropped out of the study if one the following criteria are met:

- The trial participant has ingested less than 32 tablets of rifaximin 550 mg or placebo, equal to 16 days of treatment. That is, less than rifaximin 17.600 mg or placebo, equal to 57% of planned treatment.
- The trial participant withdraws his or hers written consent.

## Follow up of possible dropouts

**Trial participants that fail to appear for weekly controls or admission to hospitals according to study design will be sought contacted by email, telephone and at their home address in that given order. If a participant is impossible to reach in this manner, he or she will be considered as dropped out of the study. Further medication will be withheld and the participants primary hospital will be informed, so as to undertake his or hers regular medication and controls.**

**We have not planned any follow-up or additional treatment for dropouts.**

## Data registration on dropouts

The following data on dropouts will be sought registered:

- Reason for drop out
- Morbidity explaining drop out
- Mortality
- All patient data collected for the time period the trial participant were included in the study, unless the patient withdraws his or hers written consent and solicits eradication of data.
- Amount of ingested Rifaximin/placebo and amount of remaining extradited Rifaximin/placebo.

## Disruption of the trial

The entire trial will be disrupted prematurely if knowledge is obtained that suggests rifaximin is unsafe or indefensible to use in patients with liver cirrhosis.

# Recruitment of participants

## Recruitment of patients at primary hospitals

The attending physician in one of the referring centres will identify patients that are eligible for the trial.

The patient will on a regular outpatient control receive oral information about the trial and be offered inclusion. Trial information and written consent is handed out. On the basis of this information the patient can choose to give his or hers written consent to participation in the trial.

The attending physician will offer the patient an information session held by the principle investigator in the outpatient clinic of the patient’s primary hospital. At this session written consent form must be signed.

It must be underlined, that all relevant procedures for diagnosing and treating the patient’s liver cirrhosis will be completed according to hospital guidelines and best practice irrespective of the patient’s inclusion in the trial.

### Referral to Hvidovre Hospital

The attending physician refers the patient to Hvidovre hospital for liver vein catheterization, with a note of trial inclusion.

The patient is hereafter referred to as the trial participant. The trial participant will receive a set of written information about procedures and trial course by mail or by the principle investigator before admission to hospital.

## Admission to Hvidovre Hospital

On the admission date, day 0 in the following, the principle investigator or a sub investigator registers the patient. Information about the trial is supplemented if necessary and written consent is verified.

# Measurements and investigations

The following flow-chart for the trial is applied. An extensive list of investigations and blood samples are given in appendix 6.

All scheduled investigations in this trial are standard procedures at the department of clinical physiology and nuclear medicine, Hvidovre Hospital. As well as blood analyses are standard procedures at the department of clinical biochemistry, Hvidovre hospital.

Standard Operating Procedures for all included investigations are therefore available to study nurses, investigators and other personnel participating in the survey and treatment of participants on the intranet for Hvidovre Hospital(26).

## Investigations on day 0

- The trial participant is fasting at admission to the hospital.
- Glucose breath test is performed to assess bacterial overgrowth.
- Hospitalisation and registration of the trial participant.
- Clinical examination by investigator or sub investigator and registration of clinical signs symptoms and basic values, That is height, weight, blood pressure, pulse, temperature.
- Routine blood samples for evaluation of kidney and liver function and possible infection (specified in appendix 6)
- To exclude occult infection: Blood culture and urinary culture.
- All women of childbearing age will have taken urine-HCG to exclude pregnancy.
- Diagnostic ascites puncture to exclude bacterial peritonitis, in case the patient has clinical ascites.
- Samples of faeces to assess bacterial composition in the gut.
- Examination of continuous reaction time (CRT) to assess possible minimal hepatic encephalopathy.
- Psychometric Hepatic Encephalopathy Score (PSE score)

All of the above blood analyses are done on peripheral blood, in total 65 ml of blood, and can be withdrawn from the same puncture site, except blood culture.

## Investigations on day 1

- The participant is fasting from the morning.
- DEXA scan is performed to determine body composition of fat, fat free mass and bone mineral composition.
- Liver vein catheterisation is performed including measurements of splanchnic haemodynamics and metabolism and systemic haemodynamics (analyses specified in appendix 6).
- Blood samples are drawn during catheterisation.
- Assessment of renal function (Cr-51-EDTA-clearance for determination of glomerular filtration rate, GFR)
- Measurements of biomarkers of renal function (specified in appendix 6)
- Samples of blood will be drawn for analysis of vasoactive hormones, cytokines, and markers of infection. (Specified in appendix 6)
- Hereafter, the participant will enter randomisation.

All blood analyses are done on liver vein blood or arterial blood from the femoral artery, in total 120 ml. Analyses for glomerular filtration rate are done on peripheral blood, this is included in the 120 ml.

## Investigations on day 2

- The first dose of active drug/placebo is given and the patients receive medication for 2 weeks.
- The participant will receive both oral and written information about how to administer the medication. The participant is discharged with a scheduled clinical control two weeks from this date.

## Investigations on day 7-10

- The patient is contacted by telephone by an investigator.
- Information on medicine ingestion and compliance is registered.
- Possible side effects, complications and wellbeing are also registered according to case report form.

## Investigations on day 14-17

- All participants are scheduled for clinical control in the outpatient clinic by an investigator.
- At the visit eventual unused tablets are counted, the patient is interviewed on compliance to treatment and ingestion of medication. Medication for the remaining trial period is handed out.
- Side effects, complications and wellbeing are also registered according to case report form.

## Investigations on day 21-24

- The patient is contacted by telephone by the study nurse or an investigator
- Information on medicine ingestion and compliance is registered.
- Side effects, complications and wellbeing are also registered according to case report form.

## Investigations on day 29-32

- At the end of the trial period, patients are re-hospitalized
- Programs of day 0 and day 1 are repeated, elaborated in appendix 6.
- Blood culture and urine culture are avoided if the participants show no signs of infection.
- A three-day treatment window is allowed to avoid admission of patients during weekends and holidays.

All blood analyses are done on liver vein blood, arterial or peripheral blood as specified above, in total 165 ml.

## Follow up

A register based follow up on patients through medical records will be performed at the end of trial, which is 1 month after last patient’s last visit. Data collection will be limited to hospital admissions and reasons hereto, complications to liver cirrhosis (esophageal bleeding, spontaneous bacterial peritonitis, hepatic encephalopathy and hepatorenal syndrome), and mortality and reasons hereto.

Hence, patients will be followed up until death, or end of trial.

# Risks and disadvantages related to investigations

Liver vein catheterisation and routine blood samples are part of the regular control and investigations of patients with liver cirrhosis. Procurement of extra blood and blood samples will be taken in addition to the patient’s admission to hospital for liver vein catheterisation. This is to avoid unnecessary blood sampling.

The study design requires the patients have all investigations repeated after 28 days to assess the effect of rifaximin. This necessitates a new admission to hospital for a minimum of 48 hours.

During blood sampling there is a small risk of developing haematoma at the puncture site. For liver vein catheterisation there is a small risk of developing haematoma at the puncture site or the femoral vein and artery. In rare cases the patient can develop vasovagal reaction during the investigation, this will be treated with an intravenous injection of atropine. Seldom the patient can develop an allergic reaction to the local anaesthetic used at the puncture site.

There are no known side effects related to chrome EDTA clearance or to glucose breath test.

Prior to liver vein catheterisation and glucose breath test the patient must be fasting for 8 hours. This can lead to mild nuisances such as thirst, headaches and dizziness. This will be sought remedied with intravenous fluids.

A DEXA scan of the body will expose the patient to a relatively small dose of radiation in the range of 0,001 to 0,01 mSv (27). In relation to investigation of glomerular filtration rate and central blood volume a small amount of radioactive isotopes will be injected in the patient, equivalent to an efficient radiation dose of 0,006 mSv and 1,8 mSv, respectively (27). For comparison background radiation in Denmark is 2-20 mSv pr. year.

# Drug information

This clinical trial will compare the antibiotic tablet rifaximin in the dosage 1100 mg daily for 28 days to tablet placebo.

Both rifaximin and placebo tablets will be delivered from Norgine Denmark free of charge. The sale name of rifaximin is Xifaxan. Each tablet of Rifaximin contains 550 mg of rifaximin. The tablets of placebo will be similar in size, shape and weight as the Rifaximin tablet.

## Rifaximin

Rifaximin, an antibacterial drug that is poorly absorbed from the gut, belongs to the group of rifamycins. Rifaximin has wide antibacterial range acting against most gram positive and negative, aerobic and anaerobic bacteria in the gut. Rifaximin acts locally in the gastrointestinal lumen, and has no clinical effect on invasive bacteria. Less than 1 % of the drug is absorbed, and the risk of interaction with other drugs is very little. Also excretion of rifaximin in urine is less than 0,4 % of administered dose.

Rifaximin treatment prevents bacterial overgrowth in the small intestine(20), thereby possibly preventing gastrointestinal infections and bacterial translocation to organs and bloodstream. Moreover, we expect the prevention of bacterial translocation to have a positive effect on the haemodynamics by decreasing hepatic venous pressure and increasing systemic blood pressure. This will be elaborated in the following.

Furthermore, rifaximin has been shown to reduce the risk of hepatic encephalopathy(21), a common complication to cirrhosis, and is approved by the FDA (U.S. Food and Drug administration) for treatment and prevention of hepatic encephalopathy.

In Denmark, rifaximin is currently approved for the treatment of travelling diarrhoea caused by non-invasive gut bacteria. Recommended dosage is 200 mg thrice daily for three days(28).

The aim of increased dosage and prolonged treatment (1100 mg daily for 4 weeks, as elaborated in the following) is to reflect the recommended dosage used for hepatic encephalopathy in USA, which has proven to be efficacious in this group of patients, when suffering from hepatic encephalopathy. Moreover, radical eradication diminishes translocation of bacteria and bacterial DNA across the gut mucosa and in to the blood stream. Hepatic venous pressure, systemic blood pressure and hepatic encephalopathy are complex modes and we expect prolonged treatment to be necessary to detect changes and achieve significant results. In previous trials of Rifaximin for the treatment of hepatic encephalopathy and rifaximin for intestinal decontamination, a daily dose of 1200 mg is administered.(8;29)

## Placebo

Placebo tablets are in appearance identical to the rifaximin tablets, but contain no active substances. A description of placebo tablets is found in appendix 10.

# Side effects, risks and disadvantages related to medication

## Possible side effects to Rifaximin

The tolerability of rifaximin has been evaluated in approximately 1000 patients in 30 clinical trials(30). Very few adverse events were reported during short-term treatment, the most common being gastrointestinal in origin, (fatigue, nausea, dizziness, pruritus and abdominal pain). It is worth noticing that these symptoms are in some ways similar to those of the patient’s underlying disease, and adverse events could have been underreported.

Prolonged treatment with high doses of rifaximin has been associated with urticarial skin reactions.

However, label information regarding rifaximin (Xifaxan) for the American market reports adverse events at either the same frequency in both rifaximin and placebo groups (31;32), or at a higher frequency in the rifaximin group (32). These reactions occur with an incidence of > 5% and relates to: peripheral oedema, nausea, dizziness, fatigue, ascites, muscle spasms, abdominal pain, anaemia, insomnia, upper abdominal pain, back pain, constipation, pyrexia, dyspnoea, nasopharyngitis and rash. Once again these symptoms are similar to the unspecific symptoms of the patient with liver cirrhosis.

In the reviewing of rifaximin for approval for treatment of hepatic encephalopathy in FDA clinical trials comprising 757 patients were evaluated(31). The adverse event profile matched that of placebo.

There is no available data on the use of rifaximin in patients with decreased kidney function. In patients with impaired liver function, no particular adjustments in dose are recommended. Data on rifaximin and its impacts on pregnancy and breastfeeding are scarce, and usage is deprecated(32).

Rare side effects (> 1/1000 to <1/100) such as increased transaminases, muscle cramps and muscle weakness, upper respiratory tract infections and increased blood pressure do appear(28).

## Possible benefits for the trial participant

Rifaximin has been shown to reduce the incidence of spontaneous bacterial peritonitis (SBP) and correct small intestinal bacterial overgrowth (SIBO) in patients with alcoholic liver cirrhosis(33;34). Intestinal decontamination may also demonstrate an improvement in liver haemodynamics(8), systemic haemodynamics and renal function(35).

These effects may contribute to the overall well-being of the patient and prevent complications to the underlying cirrhosis such as risk of infections, progression of disease, and admission to hospital.

It has also been certified that rifaximin reduces the risk of overt hepatic encephalopathy episodes(21), and improves quality of life and psychometric performance in these patients(24;36). Moreover, hospitalisation associated to HE can be reduced(31).

It is possible, but not certain, that the participants could experience some of these benefits.

This is a pathophysiological and investigational trial, and besides the mentioned benefits for the participant, he or she will also contribute to the possible development of new treatment regimens for liver cirrhosis.

## Placebo

Placebo medication is described and outlined in Investigational Medicines Product Dossier in appendix 10. We expect no benefits or disadvantages, nor risks or side effects related to placebo medication.

# Handling of trial medication

The patients will receive 550 mg of rifaximin twice daily for 28- 32 days in total. That is 1 tablet of 550 mg two times daily. The patients randomized for placebo will receive the equivalent amount of placebo tablets in the same intervals.

Treatment dose is justified in the section Drug information above, p. 17.

The medication is an oral tablet that can be ingested with a glass of water. Dosage is two times daily, morning and evening.

The regional pharmacy will pack medication in two containers for each participant, the first container comprising 28 tablets for the first 14 days of treatment and the second container comprising 34 tablets for the remaining 14-18 days of treatment.

The regional pharmacy will label medication and placebo containers according to GMP guidelines for labelling of medication for clinical trials.

All containers for the last treatment period will contain medication for 18 days, hence the 36 tablets.

At the end of the study participants will be readmitted to hospital, and due to normal workflow and weekends we cannot guarantee readmission to hospital on day 28 for all.

Therefore we have allowed a treatment window of four days at the end of the trial.

Rifaximin tablets and placebo will be similar in size, colour, shape and form.

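### The refill visit may fall as late as day 17, but the first container, started on day 2, is empty by day 15 or 16, so one to three doses can go uncovered

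*Protocol*

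**What the plan says.** *Handling of trial medication* sets twice-daily treatment for 28 to 32 days: "Dosage is two times daily, morning and evening". The pharmacy packs two containers per participant, "the first container comprising 28 tablets for the first 14 days of treatment". The second container covers the rest of the course and carries extra tablets, because the readmission day cannot be fixed.

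*Investigations on day 2* sets the start: "The first dose of active drug/placebo is given and the patients receive medication for 2 weeks". It then sets the next visit: "The participant is discharged with a scheduled clinical control two weeks from this date".

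That visit has its own section, headed "Investigations on day 14-17". There, "At the visit eventual unused tablets are counted", and "Medication for the remaining trial period is handed out". *Record keeping of medication* likewise ties dispensing to the two-weekly control. The protocol mentions no reserve tablets for the first period and no other way to obtain the second container.

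**The concern.** The first container holds exactly 14 days of tablets, with none spare, and the visit that replaces it may take place after those days have passed. A participant who takes every tablet on time and attends within the permitted window can still run out. The treatment delivered would then fall short of the continuous twice-daily course that the protocol states, for a reason that lies in the schedule and not in the participant.

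The protocol deals with the same problem at the end of treatment, where the second container is enlarged to cover a flexible readmission date. The refill visit also has a window, but the first container has no matching allowance. At stake is a small loss of exposure in the middle of the course. No power or sample-size figure depends on it.

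**Working it through.** **Inputs**
- First container: 28 tablets (*Handling of trial medication*).
- Rate: 2 tablets a day, morning and evening (same section).
- First dose: day 2, time of day not stated (*Investigations on day 2*).
- Nominal refill visit: two weeks after day 2, that is 2 + 14 = day 16 (same section).
- Permitted refill visit: day 14 to day 17 (*Investigations on day 14-17*).
- Planned doses: 56, that is 28 days × 2. This agrees with the *Dropout* section, where 32 tablets are put at 57% of planned treatment: 32/56 = 57.1%.

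**The plan's own figure.** 28 tablets / 2 per day = 14 days. It reproduces.

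**When the container runs out.** Number the dose slots so that the morning of day d is 2d and the evening is 2d + 1. With first slot s, the last tablet is taken in slot s + 27.
- Morning start on day 2: s = 4, last slot 31, the evening of day 15.
- Evening start on day 2: s = 5, last slot 32, the morning of day 16.

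**Doses missed.** For a visit on day v, dosing resumes in slot r = 2v if the visit comes before the morning dose, or r = 2v + 1 if the morning slot has passed. Doses missed = max(0, r − last slot − 1).

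| Visit day | Morning start, visit before morning dose | Morning start, visit after | Evening start, visit before morning dose | Evening start, visit after |
|---|---|---|---|---|
| 14 | 0 | 0 | 0 | 0 |
| 15 | 0 | 0 | 0 | 0 |
| 16 | 0 | 1 | 0 | 0 |
| 17 | 2 | 3 | 1 | 2 |

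As shares of 56 planned doses: 1/56 = 1.8%, 2/56 = 3.6%, 3/56 = 5.4%.

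**Distance from the outcome.** The latest refill is on day 17 and the earliest outcome day is 29: 29 − 17 = 12 days.

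**Distance from the dropout limit.** The limit is "The trial participant has ingested less than 32 tablets of rifaximin 550 mg or placebo, equal to 16 days of treatment". A participant who loses 3 doses and takes all the others has 56 − 3 = 53 tablets.

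**Supply.** *Finance and funding* gives 2520 rifaximin tablets for 38 participants and 1260 placebo tablets for 19: 2520/38 = 1260/19 = 66.3 each. *Handling of trial medication* gives the second container as 34 tablets in one place and 36 in another. Adding 3 tablets to the first container gives:
- with 34: 28 + 3 + 34 = 65 per participant, within 66.3;
- with 36: 28 + 3 + 36 = 67 per participant, above 66.3. That is 67 × 38 = 2546 against 2520, and 67 × 19 = 1273 against 1260.

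**The case against.** The strongest reply is that the start day and the pack agree: two weeks of medication are given, 28 tablets are two weeks of medication, and the control is two weeks later. That is correct. A reader might infer that the pack, the start day and the visit window all contradict one another, but the documents do not support this. Only the late end of the visit window outruns the supply.

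A second reply is that the window opens on day 14, and only day 17, one of the four permitted days, produces a certain gap. This also stands. A reader might infer that every participant is interrupted. The table shows otherwise, and the protocol gives no distribution of visit days from which to say how many would be affected.

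A third reply concerns adherence records. A reader might infer that the gap would be mistaken for non-compliance in the tablet count. At the refill visit, a participant who ran out has none of the 28 tablets left, which reads as full intake. The participant is also interviewed about intake and asked to keep a journal, so a supply gap can be recognised. The dropout limit is far away. This inference is not supported.

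What survives is narrow: on day 17, and possibly by one dose on day 16, a participant who complies fully has no tablet to take, and no other section covers the shortfall.

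**Conclusion.** The point holds as a minor inconsistency. The permitted refill window extends past the end of the first supply, so the plan allows, without requiring, a mid-course gap of one to three doses at a day-17 visit and of none or one at a day-16 visit. The worst case is 3 of 56 doses (5.4%). The effect on HVPG and GFR is probably small, since treatment has resumed at least 12 days before they are measured.

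This assumes that the day-2 dose comes from the first container, that every tablet is taken on schedule, that days are counted from admission as day 0, and that the second container is obtained only at the refill visit. The hours of the first dose and of the visit are not stated, so the result is given as a range.

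**What to change.** Reconcile *Investigations on day 2*, *Investigations on day 14-17* and *Handling of trial medication* so that the first supply and the permitted refill days agree. Which of them changes is for the sponsor to decide.

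Aligning the visit window with the supply costs an edited line and no tablets. If the pack is changed instead, it should not be assumed that the contracted supply is enough. Three extra tablets per participant fit with a 34-tablet second container (65 in total) but not with a 36-tablet one (67 against 66.3). The second-container count is a separate discrepancy, and it would have to be settled before that check can be completed.
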